**5.5. Group Allocation Method**

5.5.1. Randomization Method

Randomization codes in a 1:1 ratio for the treatment and placebo groups will be generated using the SAS statistical software package by a statistician who is not involved in data management or analysis. A block randomization design will be used, with each block including one subject in the exosome treatment group and one in the placebo group.

Drug assignment codes will be created by a statistician unaffiliated with the study. The randomization system will be available 24 hours a day. Investigational drugs will be administered according to the order of enrollment using corresponding random numbers.

The randomization codes (sealed blind codes) will be prepared in duplicate and securely stored by the principal investigator and the clinical trial pharmacy at the study institution.

Randomization and blinding will be guided by the Biostatistics Department of Hainan Medical University.

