**2.2. Secondary Objectives**

1. to evaluate changes from baseline in pulmonary function on Days 4 and 8, Week 4, and Week 12;
2. to assess HRCT imaging changes from baseline at Week 4 and Week 12;
3. to evaluate changes from baseline in six-minute walk distance (graded and actual distance) on Days 4 and 8, Week 4, and Week 12 for patients meeting criterion 5.1.2 (2) for HRCT-defined fibrotic lesions;
4. to assess changes from baseline in the St. George’s Respiratory Questionnaire (SGRQ) on Days 4 and 8, Week 4, and Week 12;
5. to assess changes from baseline in the Leicester Cough Questionnaire on Days 4 and 8, Week 4, and Week 12;
6. to assess changes from baseline in the modified Medical Research Council (mMRC) Dyspnea Scale on Days 4 and 8, Week 4, and Week 12;
7. to monitor the frequency and severity of acute exacerbations in patients with HRCT-defined pulmonary fibrotic lesions from Days 1–8, Week 4, and Week 12.

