# 5. Eligibility Criteria and Group Allocation Method

**5.1.** **Inclusion Criteria**

1. Age between 18 and 80 years (inclusive), no gender restriction.
2. Meets HRCT criteria for pulmonary fibrotic lesions:
   - 1. Manifestations include linear, rigid high-density shadows or nodular high-density shadows in the lungs.
     2. Manifestations include diffuse reticular, linear, honeycomb-like shadows or reticulonodular shadows in both lungs.
3. Typical HRCT imaging features of pulmonary fibrotic lesions within the past 12 weeks, including idiopathic pulmonary fibrosis, COPD with fibrosis, and chronic cough caused by organizing pneumonia post-COVID-19 infection.
4. Able to understand and cooperate with the pulmonary function test procedures.
5. Fully informed about the purpose, methods, and possible discomfort of the trial, agrees to participate, and voluntarily signs the informed consent form.
6. Good compliance, willing to follow the medication regimen as required by the protocol and attend follow-up examinations on time.

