# 6. Sample Size Requirement

This study is a randomized, placebo-controlled, exploratory clinical trial. A total of 24 subjects will be enrolled at the First Affiliated Hospital of Hainan Medical University, with 12 subjects assigned to the treatment group and 12 to the placebo group.

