**11.3. General and Baseline Characteristics**

(1) Demographic information, prior medication history, and comorbidities will be descriptively summarized.

(2) For quantitative variables like age, baseline comparisons between groups will be performed using grouped t-tests or Wilcoxon rank-sum tests, depending on the characteristics of the variables. For categorical variables like gender or comorbidities, comparisons will be made using chi-square or Fisher's exact tests.

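### Twenty-four patients with two HRCT lesion patterns are randomized from one unstratified list, and the comparisons the protocol names are unadjusted, leaving an avoidable risk of chance imbalance and lost precision

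*Protocol*

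**What the plan says.** Allocation (Protocol Section 5.5.1): "Randomization codes in a 1:1 ratio for the treatment and placebo groups will be generated using the SAS statistical software package", and "A block randomization design will be used, with each block including one subject in the exosome treatment group and one in the placebo group". Numbers are used in order of enrollment, and no stratification factor appears. Section 6 sets the size at 24, "with 12 subjects assigned to the treatment group and 12 to the placebo group".

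Population (Section 5.1): item 2 gives two HRCT patterns.

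- Pattern (1): "Manifestations include linear, rigid high-density shadows or nodular high-density shadows in the lungs".
- Pattern (2): "Manifestations include diffuse reticular, linear, honeycomb-like shadows or reticulonodular shadows in both lungs".

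Item 3 names several conditions, "including idiopathic pulmonary fibrosis, COPD with fibrosis, and chronic cough caused by organizing pneumonia post-COVID-19 infection".

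Use of the pattern (Section 2.2): change in six-minute walk distance is to be evaluated "for patients meeting criterion 5.1.2 (2) for HRCT-defined fibrotic lesions".

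Comparisons (Section 11.4):

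- Progression proportions: chi-square, with Fisher's exact test as an alternative for individual events.
- Times to recovery and improvement, quality-of-life scores and costs: t-test or Wilcoxon.
- IL-6: a repeated measures analysis, with t-tests at single time points.

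None of these is given a covariate or a stratum. Section 11.4 names no test for lung function or walk distance. Section 11.1 refers to a statistical analysis plan, which is not shown.

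**The concern.** The protocol treats lesion pattern as a meaningful division, because one objective applies to pattern (2) only. Yet nothing in the allocation balances that pattern between arms. With 12 patients per arm, a few patients of one pattern too many in one arm can move an average appreciably if pattern is related to outcome. It also makes the walk-distance comparison lopsided.

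Stratification has to be built into the list before the first patient, so a later analysis plan cannot supply it. The analysis can still recover precision by adjusting for pattern and for the baseline value, but the comparisons the protocol itself names do not.

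**Working it through.** The protocol gives no calculation for its 24 patients, so there is no stated figure to reproduce.

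**Inputs from the protocol.** 24 patients, 12 per arm, 1:1, blocks of two, one list, two-sided tests at 0.05 (Sections 5.5.1, 6 and 11.2).

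**Assumptions, not in the documents.** Share of patients in a pattern: 20% to 50%. Difference between patterns in a continuous outcome: 0.5, 1.0 or 1.5 within-pattern SD. Progression rates by pattern: as listed in step 5.

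**1. Chance of a difference of four or more patients.** Let D be the difference between arms in the number of patients with the pattern, and p the share with it. Each block of two adds +1 or −1 to D with probability p(1−p) each, and 0 otherwise. Summing over 12 blocks:

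| Share p | P(absolute D ≥ 4) |
| --- | --- |
| 20% | 7.1% |
| 30% | 11.6% |
| 40% | 14.3% |
| 50% | 15.2% |

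For a fixed number K with the pattern, the count in one arm is hypergeometric. With K = 12:

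P(8:4 or worse) = 1 − [C(12,6)² + 2·C(12,5)·C(12,7)] / C(24,12) = 1 − (853,776 + 1,254,528) / 2,704,156 = 0.220.

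This is the maximum. K = 8 or 16 gives 0.193. K = 11 or 13 gives about 0.10, and K = 9 or 15 about 0.09, because an odd total cannot produce a difference of exactly four.

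**2. Shift in a continuous comparison.** Shift = (D/12) × difference between patterns. For 8:4 and 1 SD: (8 − 4)/12 × 1 = 0.33 SD. The standard error of the arm difference within pattern is √(1/12 + 1/12) = 0.408 SD, so the shift is 0.33/0.408 = 0.82 standard errors.

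**3. Walk distance in pattern (2) only.** The variance factor is 1/6 + 1/6 = 0.333 at 6:6 and 1/8 + 1/4 = 0.375 at 8:4. The standard error rises by √(0.375/0.333) − 1 = 6%.

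**4. Precision gained by balancing and adjusting (K = 12).** The variance of the between-arm difference in pattern share is 4 × (12 × 0.5 × 0.5 × 12/23)/144 = 0.0435. The unadjusted standard error is √(0.1667 + 0.0435·δ²), where δ is the difference between patterns in SD. With balance and adjustment it is about 0.408.

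| δ | Unadjusted SE | Reduction |
| --- | --- | --- |
| 0.5 | 0.421 | 3% |
| 1.0 | 0.458 | 11% |
| 1.5 | 0.514 | 21% |

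This ignores the small loss of degrees of freedom and counts only the pattern term. Adjusting for the baseline value would add a gain that depends on a correlation the documents do not give.

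**5. Progression comparison, no treatment effect.** At 8:4 the expected spurious difference is (8 − 4)/12 × (difference in rates): 6.7 points for 10% vs 30%, 10.0 for 10% vs 40%, and 13.3 for 10% vs 50% or 20% vs 60%. In the last three scenarios, the exact type I error of the uncorrected chi-square test is 6.4% to 9.4% given an 8:4 split. Averaged over all allocations at a 50% share, it is 4.4% to 5.9%.

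**6. After stratification.** Blocks of two within each pattern leave at most one incomplete block per pattern. The arms then differ by at most one patient in each pattern and by at most two overall (13:11). An 8:4 split cannot occur.

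**The case against.** The strongest reply is that this is a 24-patient exploratory phase I trial with safety as its primary objective. Simple blocked randomization is legitimate there, and covariates are commonly left to the analysis plan. Much of that stands. Nothing in Section 5.5.1 is an error, and the unseen plan may adjust, so the point is limited to the comparisons the protocol itself names.

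Four stronger readings are tempting, and the documents do not support them.

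- A reader might infer that the three diagnoses run opposite courses over 12 weeks. Section 5.1 only lists them. The argument needs no more than that pattern may be related to outcome, and the size of that relation is an assumption.
- A reader might take the baseline tests in Section 11.3 as the plan's safeguard, certifying an 8:4 split as balanced. Such a split is indeed non-significant (Fisher p = 0.22, Pearson p = 0.10). But Section 11.3 does not name lesion pattern or diagnosis and attaches no consequence to any result.
- A reader might quote 22% as the risk. That is the worst case.
- A reader might call the unadjusted tests invalid. Averaged over allocations, the type I error stays near 5%.

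Two practical objections also stand. The HRCT sub-items are not stated to be exclusive (both mention linear shadows), so they need a yes/no rule before they can serve as strata. The documents do not map diagnoses to patterns, so stratifying by pattern does not guarantee balance by diagnosis. Covariate adjustment also suits the progression proportion poorly: it has no baseline value, and with 12 per arm and few events a model may fail to converge.

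**Conclusion.** The point holds as a cheap improvement to design and analysis. It does not show a flaw that invalidates the trial. One unstratified list leaves roughly a 7% to 15% chance, and at most 22%, of a difference of four or more patients in a lesion pattern. Such a split would shift a continuous comparison by 0.33 SD if the patterns differ by 1 SD, and would leave walk distance compared in 8 against 4. Balancing and adjusting would narrow standard errors by about 3% to 21% for pattern differences of 0.5 to 1.5 SD. The pattern shares and pattern effects are assumptions. What the documents themselves establish is the unstratified list, the mixed population, the objective restricted to pattern (2) and the unadjusted named tests.

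**What to change.** 1. **Analysis (Section 11.4).** For continuous efficacy outcomes (lung function, walk distance, SGRQ, LCQ, IL-6), specify a baseline-adjusted comparison. This can be ANCOVA or a repeated-measures model with the baseline value and lesion pattern as covariates. It replaces the plain t-test or Wilcoxon where Section 11.4 names one, and is fixed in advance whatever the baseline table shows. Where walk distance is analyzed in pattern (2) only, the pattern term drops out. Leave the sparse progression comparison without covariates.

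2. **Randomization (Section 5.5.1).** Before randomization, record one exclusive class from the eligibility HRCT (pattern (2) present: yes or no) and generate one list per class. With the planned blocks of two, this limits the imbalance to one patient per class.

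**Cost.** One more list from the same program and one extra item recorded before allocation. The baseline values are already collected at D0 in Table 1. In a single-time-point model with all 24 patients, residual degrees of freedom fall from 22 to 20 with both covariates, or to 21 with one. The overall split may end at 13:11. If recruitment has already begun, only the analysis change can be applied in full, and it should be fixed before any unblinded comparison.

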5.5.2. Blinding

One research coordinator will be designated to maintain and distribute randomization numbers, prepare investigational drugs, and coordinate information among the study staff.

One study physician will be designated for patient management and data recording.
One study nurse will be responsible for administering the investigational product and monitoring safety.

Trained physicians will follow up with patients and perform additional diagnostics.

All members of the research team will remain blinded to each other’s assessments throughout the study.

5.5.3. Investigational Exosome Preparation (Derived from Human Umbilical Cord Mesenchymal Stem Cells)

Exosome nebulization solution: 2 ml/vial, containing 2×10⁹ particles.

The investigational exosome product is provided by Shanghai GenWay Cell & Tissue Storage Co., Ltd. It is derived from mesenchymal stem cells (MSCs) cultured and purified from donated neonatal umbilical cord tissue (see Section 5-0 for donor screening criteria and informed consent form, and Section 5-1 for perinatal tissue handover information). The MSC supernatant is further purified to obtain exosomes.

Informed consent is obtained from all healthy donors. Any remaining investigational products will be uniformly retrieved and destroyed after study completion.

A dedicated management system is established for the storage and distribution of investigational products. Products are delivered directly to designated personnel in the clinical research department by staff from Shanghai GenWay Cell & Tissue Storage Co., Ltd., with proper documentation for product handover.

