# Method of Administration, Dosage, Timing, and Course of Treatment for the Extracellular Vesicle (EV) Preparation

**7.1. Registration, Usage Records, Delivery, Distribution Method, and Storage Conditions of the EV Nebulized Solution**

1. After the EV product is fully prepared and passes quality control, laboratory personnel shall complete the **EV Nebulization Application Form** and submit it to the investigators. Both parties confirm relevant information about the EV product (including subject name, hospital admission number, EV product batch number, and quality inspection report), agree on the nebulization schedule, and sign for confirmation.
2. Laboratory personnel shall complete the EV Nebulized Solution Release Application Form, which must be signed by the quality control officer. The form is then submitted to the warehouse manager. Upon reconfirming the relevant EV nebulized solution information (including subject name, hospital admission number, EV nebulization batch number, and quality inspection report), both parties sign the EV Nebulized Solution Release and Handover Form. The refrigerated box containing the EV nebulized solution is then handed over to the laboratory personnel.
3. The laboratory personnel transport the refrigerated box containing the EV nebulized solution to the laminar flow ward. Together with the investigators, they reconfirm the EV nebulized solution information (including subject name, hospital admission number, batch number, and quality inspection report) and sign the EV Nebulized Solution Handover Record Form, after which the solution is handed over to the investigators.
4. **Storage condition:** 2°C–8°C.

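### Fixed, disclosed blocks of two, with subject-named EV forms signed by investigators, make up to 12 of 24 allocations deducible, and no assessor is stated to be blinded to allocation

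*Protocol*

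**What the plan says.** Section 4.1 describes one centre, 1:1 randomization and a single-blind design, without saying who is blinded. Section 5.5.1 fixes the block composition in print, "with each block including one subject in the exosome treatment group and one in the placebo group", and ties treatment to entry order: "Investigational drugs will be administered according to the order of enrollment using corresponding random numbers". Section 6 gives the total of 24, "with 12 subjects assigned to the treatment group and 12 to the placebo group".

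On custody, section 5.5.1 states: "The randomization codes (sealed blind codes) will be prepared in duplicate and securely stored by the principal investigator and the clinical trial pharmacy". One statistician, outside data management and analysis, generates the list, and a statistician unaffiliated with the study creates the drug codes.

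Section 5.5.2 gives a coordinator the randomization numbers and the preparation of study drug. Its only sentence on what staff are blinded to is: "All members of the research team will remain blinded to each other’s assessments throughout the study". Knowledge of treatment is not mentioned.

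Under section 7.1 the investigators receive an EV application form: "Both parties confirm relevant information about the EV product (including subject name, hospital admission number, EV product batch number, and quality inspection report". They agree the nebulization schedule, sign, and later reconfirm the same details at the ward and receive the EV solution. No equivalent is described for saline, which section 7.2 lists with its own presentation and storage condition.

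**The concern.** With blocks of two, the second member of each pair has no randomness left once the first is known. The forms in section 7.1 reveal the first member either way: a form means EV, and the absence of a form points to saline. If the person enrolling has this information, entry of the second member can be steered, consciously or not.

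The protocol leaves room for that. Exclusions 19 and 20 in section 5.2 (poor compliance, and any condition of concern to the researcher) are matters of judgement. Knowledge of the arm can also act after entry. Investigators decide whether a laboratory finding is clinically significant (10.1), assign the causality category that feeds the adverse-reaction rate (10.3), and may withdraw subjects (5.3). Section 10.4 keeps events attributed to disease progression out of the SAE count.

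Safety is the primary objective (2.1). With 12 per arm, one steered enrolment or one reclassified subject moves an arm's rate by 1/12, or 8.3 percentage points. No analysis can undo this afterwards.

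**Working it through.** **Inputs.** Block of two, one per arm, and treatment in order of enrolment (5.5.1); N = 24 as 12 + 12 (6); first 4 subjects entered one after another, then a safety assessment (7.2).

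**The plan's own figure.** 24 / 2 = 12 blocks, each with 1 EV and 1 placebo, gives 12 + 12. This agrees with section 6.

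**Predictability when past allocations are known.** For a block of size 2m, a guesser names the arm with more places left.
- Expected deterministic fraction: 1/(m + 1).
- Expected correct guesses per block: m + 2^(2m−1)/C(2m, m) − 0.5.

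Per block:
- m = 1: fraction 1/2, so 1 of 2 deterministic; correct = 1 + 2/2 − 0.5 = 1.5.
- m = 2: fraction 1/3, so 1.333 of 4; correct = 2 + 8/6 − 0.5 = 2.833.
- m = 3: fraction 1/4, so 1.5 of 6; correct = 3 + 32/20 − 0.5 = 4.1.

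Over 24 subjects:

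| List | Deterministic | Correct guesses |
|---|---|---|
| Blocks of 2 (12 blocks) | 12 (50%) | 18.0 (75%) |
| Blocks of 4 (6 blocks) | 8 (33.3%) | 17.0 (70.8%) |
| Blocks of 6 (4 blocks) | 6 (25%) | 16.4 (68.3%) |
| 4+4+4+6+6, sizes known | 3 × 1.333 + 2 × 1.5 = 7 (29.2%) | 3 × 2.833 + 2 × 4.1 = 16.7 (69.6%) |
| One permutation of 24 | 1.85 (7.7%) | 14.6 (60.8%) |

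**How far the blocks-of-two figures depend on knowledge.** Let p be the share of pairs in which the enroller knows the first allocation before the second subject consents. The protocol does not give p, so it is an assumption. Deterministic allocations = 12p; correct guesses = 12 × (1 + 0.5p).
- p = 0: 0 deterministic, 12 of 24 correct (50%).
- p = 0.5: 6 deterministic, 15 of 24 correct (62.5%).
- p = 1: 12 deterministic, 18 of 24 correct (75%).

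The first 4 subjects form two complete pairs. Each is observed for 24 hours after the first treatment before the next begins, so the condition is easily met for those two pairs if the enroller sees the forms.

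**Effect of alternative lists on the section 7.2 safety assessment.** Blocks of two, or a first block of 4, guarantee 2 EV and 2 placebo among the first 4. A single 12:12 permutation does not:
- 0 EV: C(12,4)/C(24,4) = 495/10,626 = 4.7%.
- 1 EV: 12 × C(12,3) = 2,640 of 10,626.
- 0 or 1 EV: 3,135/10,626 = 29.5%.

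The least predictable list would therefore often leave that assessment with almost no EV experience.

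**The case against.** The following can fairly be said for the plan.

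- **The predictability is conditional.** Section 7.1 speaks of the investigators and does not say that they are the people who enrol. After the first 4 subjects, both members of a pair could enter close together. This stands: 50% and 75% are ceilings.
- **A reader might infer that the principal investigator's copy discloses the list.** The documents do not support that. The codes are described as sealed, and they come from statisticians kept apart from the study's data work. Custody by the principal investigator is a weak safeguard, not disclosure.
- **A reader might infer that all outcome assessors know the arm.** The documents do not show this either. No HRCT or lung-function reader is named, and nothing says the follow-up physicians sign the EV forms. The SGRQ, LCQ and mMRC are answered by patients, who are presumably the blinded party. What stands is that the protocol is silent on assessors' knowledge of allocation.
- **Single-blinding is a declared choice in a small exploratory trial.** That is so, but it does not require blocks of two or investigators who sign arm-revealing forms. The trial also compares arms at p ≤ 0.05 (11.2), which relies on a fair allocation.
- **Larger blocks gain little.** Correct guesses fall only from 75% to about 70% while past allocations remain visible. This stands, and is why concealment must accompany the change of list.

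**Conclusion.** The point holds in this form. As written, sections 5.5.1 and 7.1 together make the second allocation of each pair deducible by anyone who knows the first. The upper bound is 12 of 24 allocations deterministic and 75% guessed correctly, against 50% with no information. It rests on the enroller knowing all past allocations, and it shrinks in proportion to the share of pairs in which that is so.

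Separately, section 5.5.2 makes no provision for blinding AE-causality or outcome assessors to allocation. Loss of that blinding is demonstrated only for investigators who sign the EV forms; for follow-up physicians and for HRCT and lung-function readers it is an omission. Sections 5.5.2 and 7.1 also need reconciling, since one gives drug preparation to the coordinator and the other hands the EV solution to investigators. All of this is fixed in the protocol itself, and should be corrected before enrolment.

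**What to change.** 1. **List.** Replace blocks of two in 5.5.1 with mixed blocks of 4 and 6 summing to 24, for example 4+4+4+6+6. Make the first block a 4, so that the section 7.2 assessment of the first 4 subjects still covers 2 EV and 2 placebo, and randomize the order of the rest. Remove block sizes from the site protocol and keep them with the independent statistician.
2. **Concealment.** Route the section 7.1 forms and handover, for both arms, to the coordinator already designated in 5.5.2. Both arms already nebulize 8 ml (2 ml EV plus 6 ml saline, against 8 ml saline), so the prepared doses can be labelled and presented identically.
3. **Blinding statement.** State in 5.5.2 that the enrolling physicians, the physicians who assess AEs and outcomes, and the existing HRCT and lung-function readers are not told the allocation.

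Cost: a new list, re-routed forms and a short text change, with no extra staff. Interim balance loosens slightly: the arms can differ by up to 2 within a block of 4 and 3 within a block of 6, against 1 now. The final split stays 12:12.
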